#### Blinding

This is an unblinded study as the study condition to which each participant has been assigned can be deduced by looking at the interventions that they have received. We considered conducting a blinded analysis. However, since all the information to unblind the assigned groups would be required, we determined that there was no way of practically conducting a blinded analysis and determined that all the analyses will be unblinded.

#### Randomization

We will randomly assign 512 participants representing three clinics to one of 16 study conditions (Table 2) using a permutation allowing for the study conditions to include an equal number of participants, which is 32 (16*32 = 512). We developed the random assignment of participants in Stata v.14 using *runiform* and *rank* functions. The randomization sequence is concealed from all study staff involved in recruitment, enrollment, and randomization. Once eligibility has been determined, designated study staff will randomly assign participants to a study condition, using the REDCap electronic database.

#### Data and statistical analysis

Study staff will collect data directly onto the REDCap database using password-protected tablets. The REDCap database was designed with automated internal checks to ensure data entered are accurate and complete. In addition, the site follows a data management plan, which outlines quality control and quality assurance practices. All participants will be assigned a study identifier and data for analysis will only be identified through this number. All documents that contain personal identifiers will be kept in locked cabinets with limited access.

We will employ a series of descriptive and inferential statistical methods and techniques for data analysis. For dataset preparation, missing baseline data on socio-demographics will be imputed using a single imputation technique if the proportion missing is <10% or using a multiple imputation technique if the proportion missing is ≥10%, respectively. In cases of missing viral load data, we will treat the result as detectable, in accordance with our primary intention-to-treat (ITT) analytic approach, similar to other studies [3, 63]. For missing adherence data, the most recent month’s adherence will be used to estimate single-month adherence; for cumulative calculations, available data over the period will be used.

To estimate treatment effects, we will adopt an ITT analytic approach and all 512 participants will be analyzed according to their randomized condition. The primary outcome is viral suppression at 24 months (see Table 1), measured as a binary variable, to allow us to assess a sustained post-intervention effect [64]. We will use logistic regression to estimate main and interaction effects on the odds of viral suppression. We will use an exchangeable correlation matrix, accounting for clustering by health facility for all analyses. Participants’ receipt of intervention components will be effect-coded. That is, following Kugler et al., [65] we will code participants’ receipt of an intervention component as 1, and nonreceipt as −1. To estimate the main effect of an intervention component, we will multiply the coefficient term by two and exponentiate it (i.e., implementing the mathematical operation as follows: Exp(2*coefficient term)). We will use the same approach to estimate interaction effects between components. Similarly, we will use logistic regression to estimate effects of components on secondary outcomes measured as a binary outcome (viral load at month 12; adherence; retention). We will use linear or Poisson regression to estimate effects of components on outcomes measured as a continuous variable (e.g., mean change in viral load from month 0 to 12 and month 0 to 24) or count variable (e.g., days of unsuppressed virus), respectively. We will compare dropout rates and characteristics of participants who drop out or are lost to follow-up with those retained to assess potential for bias. We will also assess evidence of contamination by examining data from our detailed REDCap records and texting logs, using any such evidence when interpreting data on outcomes. Moderating effects will be explored through regression modeling following Hayes [66]; mediators will be assessed using the approach by Valeri and VanderWeele, which allows for logistic modeling, and sensitivity analyses will be conducted on key assumptions per Imai [67, 68]. For all quantitative analyses, we adopted REDCap for data capture and SAS for data analysis [69].

IDIs will be analyzed for potential mediating and moderating influences over time (e.g., reductions in substance use and stigma) using content analysis [70], involving iterative transcript review, label development, creation of operational definitions, and codebook development. We will doubly code ~20% of interviews and discuss discrepancies to achieve consensus. After codebook completion, transcripts will be coded in Dedoose (version 8.3.11). We will identify direct statements to illustrate findings.

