### Optimization phase

This phase of the study—SUSTAIN—involves a fractional factorial design and regression analysis adjusted for clustering by clinic to accomplish three aims: (1) to determine the relative efficacy of five intervention components on the primary and secondary outcomes (described below); (2) to assess implementation, service, and client outcomes pertinent to each intervention component; and (3) to model the multi-component intervention optimized for cost-effectiveness and implementation success.

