#### Study setting

This study is taking place in three City of Cape Town clinics in the Klipfontein and Mitchell’s Plain health districts in South Africa. Each of these clinics serves a population with a high prevalence of HIV. Although precise numbers are not available, prevalence in these districts is believed to be higher than in Cape Town generally which was estimated to be 9.5% in 2017 [51]. Each clinic provides free ART services delivered by doctors, clinical nurse practitioners, and registered nurses [26].

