#### Eligibility criteria

Study participants must be adolescents aged 16–17 years or adults ≥18 years of age, who are presenting to the clinic for initiation of ART. Study participants must be willing and able to sign informed consent or, in the case of minors, informed assent with parents willing to sign informed consent. They must have a working cellphone and be willing to receive study-related text messages. They must also be willing and able to comply with study procedures, including using an EAM and providing current contact information. We aim to enroll 512 participants (roughly 170 per clinic) between March 2022 and February 2024.

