#### Sample size

We anticipate we will need 512 participants for this study to ensure the power to detect a clinically meaningful individual effect of intervention components on HIV viral suppression. Our sample size of 512 combines two estimates: (a) the number of individuals needed to detect a clinically significant sized effect in HIV viral suppression rate due to receipt of an intervention component; and (b) the number of individuals who we may lose over the course of the study. To elaborate, first, we assume we will have a 14-percentage point increase in viral suppression in participants receiving a specific intervention component compared to those who receive the standard of care alone. Our estimate of 14 percentage point increase is based on recent work at Cape Town clinics indicating suppression rates of 51–79% at month 12 post-initiation of ART [4]. Therefore, using the baseline HIV viral suppression rate of 60%, endline rate of 74%, a two-sided alpha of 0.05 and 80% power, and intraclass coefficient component (ICC) of 0.15, we calculated that we will need a sample of 458, using PS Power and Sample Size Calculations [58]. While we do not know the ICC for each clinic to inform the design stage (for the sample size calculation in a RCT design involving participants representing three clinics), we conservatively assumed they are 0.15, based on recent studies showing ICC estimates ranging between 0.01 and 0.12 [59–61]. To account for lost to follow-up of up to 10% (based on site experience in other recent studies), we will need to recruit a total of 510 participants, which we increased to 512 to be able to sample an equal number of participants across three clinics and 16 study conditions. For secondary outcomes, this sample size will allow us to detect differences in ≥90% adherence and in retention of 11–15%, a meaningful range that is reasonable given other studies [22, 62].

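### With only three clinics, the exchangeable-correlation model has valid tests under model-based standard errors but not under cluster-robust ones, and the article does not say which will be used

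*Protocol article*

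**What the plan says.** The Data and statistical analysis section of the protocol article sets the primary model: "We will use logistic regression to estimate main and interaction effects on the odds of viral suppression". It then fixes the treatment of clinic: "We will use an exchangeable correlation matrix, accounting for clustering by health facility for all analyses". The Optimization phase section says the same more briefly: "regression analysis adjusted for clustering by clinic". Logistic regression with an exchangeable correlation by facility is, on its ordinary reading, a marginal model fitted by generalized estimating equations (GEE) with the clinic as the cluster.

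The number of clusters is given under Study setting: "This study is taking place in three City of Cape Town clinics". Eligibility criteria gives roughly 170 participants per clinic. Assignment is at participant level: "We will randomly assign 512 participants representing three clinics to one of 16 study conditions".

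The article names SAS as the software. It names no procedure, variance estimator, small-sample correction or reference distribution, and no fixed clinic effect.

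**The concern.** Models defined by a working correlation are usually reported with sandwich standard errors, which estimate the variance from the spread between clusters. That works with many clusters. With three, the estimate rests on two independent pieces of information, so it is biased low and very unstable, and a normal reference ignores both faults.

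Clinic is also not the unit of assignment here. Conditions are crossed with clinics, so clinic is a baseline factor whose differences can be removed directly.

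The tests of main effects, interactions and secondary outcomes would all be affected. The trial exists to choose components for a package, and the Cost-effectiveness analysis section carries forward the components found efficacious. A test with a true error rate near 25% would often put an inert component on that list.

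**Working it through.** **Inputs.** Three clinics (Study setting), about 170 each (Eligibility criteria), and 512 individuals in 16 conditions of 32 (Randomization). By Table 2, each component is therefore on in 256 and off in 256. Sample size gives 60% against 74%, with "endline rate of 74%, a two-sided alpha of 0.05 and 80% power, and intraclass coefficient component (ICC) of 0.15", and cites "recent studies showing ICC estimates ranging between 0.01 and 0.12". Assumed here: overall suppression of 67% under the null (midway between 60% and 74%) and ICCs of 0 to 0.15 on the logit scale, which span the article's values. Clinic and condition were permuted independently, so stratification by clinic is not assumed.

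**Step 1: the plan's own sample size.** The two-proportion formula with pooled variance gives

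(1.96 × √(2 × 0.67 × 0.33) + 0.8416 × √(0.60 × 0.40 + 0.74 × 0.26))² / 0.14² = 175.9, so 176 per level and 352 in total.

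Multiplying by 1 + (3 − 1) × 0.15 = 1.30 gives 457.6, so 458, as stated. This N is used in Step 4.

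**Step 2: analytic error rate of the robust test.** With three equal clusters, the uncorrected sandwich statistic behaves as √(3/2) times a t variable with 2 df. For 2 df, P(|t| > x) = 1 − x/√(2 + x²).

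- Normal reference: x = 1.96 × √(2/3) = 1.600, so P = 1 − 1.600/√(2 + 2.561) = 25.1%.
- t reference with 2 df: x = 4.303 × √(2/3) = 3.513, so P = 1 − 3.513/√(2 + 12.343) = 7.2%.

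Neither the ICC nor the number of model parameters enters.

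**Step 3: simulated error rates.** Table 2 design, no component effects, main-effects model, 2,000 trials per ICC. Entries are percentages per component, except the third column, which is per trial. The Monte Carlo standard error of the robust rates is about 0.5 points.

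| ICC | Robust SE, normal | At least one of five (robust, normal) | Robust SE, t with 2 df | Same GEE, model-based SE | Logistic with clinic indicators |
|---|---|---|---|---|---|
| 0 | 25.4 | 77.5 | 7.3 | 5.1 | 5.1 |
| 0.01 | 25.7 | 78.4 | 7.3 | 4.8 | 4.9 |
| 0.05 | 25.3 | 76.5 | 7.5 | 4.8 | 5.1 |
| 0.12 | 25.6 | 76.8 | 7.9 | 4.9 | 5.1 |
| 0.15 | 26.0 | 77.9 | 7.7 | 4.6 | 5.1 |

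Independence would give 1 − 0.749⁵ = 76% for at least one of five, in line with the third column.

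With all two-way interactions (16 parameters, about 1,000 trials each at ICC 0.01 and 0.15), the robust normal test gave 25.6% and 26.0%, the model-based GEE 5.9% and 5.3%, and clinic indicators 6.1% at both. The robust inflation is thus the same with 6 or 16 parameters. The small excess over 5% in the other two columns is minor beside it.

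**Step 4: power.** 60% against 74%, N = 458, 1,500 trials each at ICC 0, 0.05 and 0.15:

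- clinic indicators: 88.8%, 87.1%, 86.0%
- GEE with model-based SE: 88.9%, 86.6%, 85.1%
- GEE with robust SE and t on 2 df: 56.1%, 54.7%, 51.1%

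**Step 5: joint tests.** The three clinics' score contributions sum to zero at the solution, so the robust covariance has rank 2, as found in every simulated trial where rank was checked. A joint robust test of five components needs rank 5 and cannot be formed.

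**The case against.** The strongest reply is that the article fixes a working correlation and nothing more. The variance estimator is a detail that a condensed article may leave to the analysis plan, and under model-based standard errors the stated main-effects model holds 4.6 to 5.1% with 85 to 89% power. That stands. A reader might infer that the plan, as written, has a 25% error rate. The documents do not support this, because they never say that sandwich standard errors will be used.

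A reader might also infer that the error comes from having fewer clusters than parameters. It does not: 6 and 16 parameters give the same rate. The rank deficit limits joint tests only.

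The consequence should not be overdrawn either. The choice of standard error does not move the point estimates. The Cost-effectiveness analysis section states no p-value rule for inclusion and leaves the final choice to the core team, weighing effect, cost and implementation. The package is then to be tested in a later randomised trial, where an inert component could still be exposed.

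What the reply does not remove is that sandwich inference is the usual companion of a working-correlation model, nothing in the text excludes it, and the clustering method is fixed for all analyses. A low observed ICC gives no protection, because the inflation is the same at ICC 0.

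**Conclusion.** The concern holds conditionally. Accounting for three clinics through an exchangeable correlation leaves the error rate of the main-effects tests anywhere from about 5% to about 25% per component, depending on an estimator the article does not name. The upper figure assumes uncorrected cluster-robust standard errors with a normal reference. Moving to a t reference with 2 df is not a rescue: it leaves 7.3 to 7.9% error and power of 51 to 56% against the planned 80%. The cause is the number of clusters, not the ICC or the size of the model.

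Only the binary logistic outcome was simulated. The analytic argument in Step 2 does not depend on outcome type, but the linear and Poisson secondary models were not checked by simulation.

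This should be settled in writing before the month-24 analysis. It is not evidence that the planned analysis is certain to be invalid.

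**What to change.** Preferred: replace the clinic-level exchangeable correlation with clinic as a fixed factor (two indicator variables) beside the effect-coded components. Use model-based standard errors for the logistic models and participant-level robust standard errors for the linear and count models. In the main-effects simulations this held 4.9 to 5.1% error, with 86 to 89% power at N = 458, and validity no longer hangs on an unstated choice.

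Alternative: keep the exchangeable model and state that tests and intervals will use model-based, not cluster-robust, standard errors.

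The preferred change costs a sentence of analysis wording, two degrees of freedom and no new data. It also changes the estimand: the odds ratio becomes conditional on clinic instead of population-averaged, and the two differ when suppression varies between clinics. The report should say which is given. The alternative keeps the population-averaged odds ratio.

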**Fig. 2 Fig2:**
[figure not shown]
Theoretical framework of the SUSTAIN study. Abbreviations. OTR, outreach. PRM, pharmacy refill monitoring. EAM, electronic adherence monitoring

Prior to beginning this study, the team carried out the preparation phase of MOST. We partnered with local officials and clinical staff in Cape Town to review evidence for adherence interventions and conduct formative research to identify the most effective, acceptable, and feasible intervention components for patients and providers. These components formed the basis for a pilot study [50] in which we used in-depth interviews (IDIs) with patients and focus groups with providers to determine the most preferred intervention components to advance to the next phase. For our final study design for the optimization phase, we incorporated the two most preferred support strategies identified in our pilot study: (a) weekly check-in texts (S1); and (b) enhanced peer support, using motivational interviewing (MI) (S2). We also included three means of rapidly identifying and reaching out to nonadherent patients: (1) Early call to the patient (e.g., within a week) after a standard viral load test showing an unsuppressed virus (M1); (2) patient pharmacy refill monitoring, with an early call to the patient after a missed refill (M2); and (3) real-time EAM, again with an early call to the patient if doses are missed (M3). These five intervention components are described in Table 1.

**Table 1 Tab1:** Intervention components

**Component**	**Component type**	**Frequency**	**Method of delivery**
Standard of Care (SoC): Informing the patient of the VL result at their next clinic visit and initiating counselling	SoC	At the next visit after month 4 and month 12 after ART initiation	In-person at the clinic
M1: Call to the patient after unsuppressed VL on routine testing	Adherence monitoring	At month 4 and month 12 after ART initiation	Direct phone calls
M2: Pharmacy refill monitoring and call to the patient	Adherence monitoring	Monthly or 2 monthly for 12 months, depending on clinic visit schedule	Direct phone calls
M3: Electronic adherence monitoring and call to the patient	Adherence monitoring	Reviewed weekly	Direct phone calls
S1: Weekly check-in text messages	Adherence support	Weekly for 12 weeks once suboptimal adherence detected	Automated weekly text messages with option to reply

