S2: Peer support (Basic or enhanced)	Adherence support	Monthly for 3 months once suboptimal adherence detected	Basic: One-on-one or group adherence sessions delivered by clinic counsellors Enhanced: One-on-one motivational interviewing delivered by study staff

Abbreviations: *SoC*, standard of care; *VL*, viral load; *ART*, antiretroviral therapy

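### The analysis section promises intention-to-treat but codes each component by receipt; the regressor should be defined as the assigned level

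*Protocol article*

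**What the plan says.** Data and statistical analysis makes two statements about the primary model in the same paragraph.

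- The principle is intention-to-treat: "all 512 participants will be analyzed according to their randomized condition".
- The coding rule is that participants' "receipt of intervention components will be effect-coded", and then that the analysts will code "receipt of an intervention component as 1, and nonreceipt as" −1. For a main effect the analyst will "multiply the coefficient term by two and exponentiate it". For interactions: "We will use the same approach to estimate interaction effects between components".

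Table 1 says when support is delivered. Weekly texts (S1) run "Weekly for 12 weeks once suboptimal adherence detected". Peer support (S2) runs "Monthly for 3 months once suboptimal adherence detected". The M1 call follows an unsuppressed viral load, the M2 call a missed refill, and the M3 call missed doses.

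The Intervention components section makes M1, M2, M3 and S1 on/off factors, and S2 a basic or enhanced factor. Table 2 fixes every level by randomised condition.

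**The concern.** In many trials receipt and assignment nearly coincide, and loose wording does no harm. Here they differ by design. A participant assigned to texts who never triggers support receives none, and under a literal reading would be coded −1 together with those assigned to no texts. Those coded +1 would be only the participants already detected as struggling. The contrast would then compare people in difficulty with a mixture of everyone else, and randomisation would no longer protect it.

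The coding sentence is the one a programmer would implement. Delivery is recorded (the paragraph itself refers to REDCap records and texting logs), so a receipt variable could be built. All analyses are unblinded, which is a further reason to fix the definition in advance. The Cost-effectiveness analysis section says that poorly performing elements will be eliminated, so a main effect with the wrong sign could remove a useful component from the package.

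Receipt and nonreceipt also do not describe S2. A participant randomised to basic counselling who triggers support does receive counselling, so only the assigned level gives an unambiguous code.

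**Working it through.** The article gives no figure for this point, so there is nothing of its own to reproduce. The check has three parts.

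**1. Coding by assignment.** 512 participants over 16 conditions is 32 each. Each component is at its + level in 8 conditions, so each main effect compares 8 × 32 = 256 with 256. With Table 2 coded ±1 by assignment, all five columns are balanced and mutually orthogonal. Coding by assignment therefore gives a clean randomised contrast for every component.

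**2. Coding by actual receipt.** The inputs below are assumptions, because the article states neither the share triggering support nor suppression by trigger status. Let q be the triggered share, a the suppression in those never triggered, b the suppression in those triggered without the component, and c the suppression in those triggered with it. Half are assigned to the component.

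- Suppression in receivers = c.
- Suppression in non-receivers = {0.5[(1−q)a + qb] + 0.5(1−q)a} / {0.5 + 0.5(1−q)}.

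*A component with no effect* (a = 0.80, b = c = 0.40; receivers' odds 0.40/0.60 = 0.667):

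| q | Non-receivers suppressed | Odds | Receipt-coded OR |
|---|---|---|---|
| 0.30 | (0.34 + 0.28)/0.85 = 0.729 | 2.70 | 0.25 |
| 0.40 | (0.32 + 0.24)/0.80 = 0.700 | 2.33 | 0.29 |
| 0.50 | (0.30 + 0.20)/0.75 = 0.667 | 2.00 | 0.33 |

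The correct value is 1.00 throughout.

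*A useful component* (q = 0.40, true odds ratio 1.9 in those triggered): receivers' odds are 0.667 × 1.9 = 1.267, so c = 0.559. By receipt the odds ratio is 1.267/2.333 = 0.54. By assignment, suppression is 0.6 × 0.80 + 0.4 × 0.559 = 70.4%, against 0.6 × 0.80 + 0.4 × 0.40 = 64.0%.

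*Sensitivity of the sign*, with q from 30% to 60%:

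| a / b / c | OR by assignment | OR by receipt |
|---|---|---|
| 85 / 35 / 55% | 1.36–1.66 | 0.38–0.70 |
| 80 / 40 / 54% | 1.22–1.42 | 0.44–0.69 |
| 75 / 50 / 64% | 1.22–1.44 | 0.74–0.99 |
| 70 / 60 / 74% | 1.22–1.48 | 1.32–1.48 |

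The sign reverses in the first three rows and not in the last, where triggered participants start only 10 points lower.

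*Simulation* of the five-component logistic model on the Table 2 design (1,000 runs, n = 512, a = 80%, b = 40%, c = 54% for S1, no effect of the other components). By assignment, the median S1 odds ratio was 1.23, 1.29 and 1.35 at q = 30, 40 and 50%. With S1 and S2 coded by receipt it was 0.65, 0.71 and 0.77, and a nominally significant harm appeared in 32%, 30% and 23% of runs, against 0.1% by assignment. These medians are nearer 1 than the two-group values because S2, also coded by receipt, absorbs part of the trigger effect.

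**3. Interaction scale.** With logit = b0 + b1x1 + b2x2 + b12x1x2 and ±1 coding, the odds ratio for x1 is exp(2b1 + 2b12) at x2 = +1 and exp(2b1 − 2b12) at x2 = −1. Their ratio is exp(4b12). Exp(2b12) is its square root: a ratio of odds ratios of 2.0 corresponds to exp(2b12) = 1.41.

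**The case against.** The strongest reply is that receipt here simply means the assigned level. The intention-to-treat sentence governs the paragraph. The Sample size section uses receipt of a component for the contrast on which the trial is powered, and the Discussion speaks of participants being randomised to receive basic counselling. Departures in delivery are handled separately: evidence of contamination informs interpretation and does not recode the regressors. This argument largely stands. A reader might infer that the trial has settled on coding by receipt in place of assignment; the documents do not support that, and assignment is the likelier intent.

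A reader might also infer that receipt of any component marks a failing participant. That is too broad. Refill monitoring (M2) and weekly review of electronic adherence (M3) apply to everyone assigned, and only the call is triggered. The argument is strongest for S1 and S2.

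Nor do the documents support a claim that the sign of a useful component would reverse. The trigger rates are unstated, and in the last row of the sensitivity table it does not.

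On interactions, 2b is a recognised factorial convention (half the difference between simple effects), and the article never calls Exp(2b) a ratio of odds ratios. Tests and model-predicted suppression are the same on either scale. It would go too far to say that the rule understates interactions in the cost-effectiveness model, since the article does not say that Exp(2b) feeds it.

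What survives is that the operative sentence names a different variable from the principle above it, and that its two categories do not fit S2.

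**Conclusion.** The concern holds as an internal contradiction in the definition of the primary regressor. It does not establish that the trial will be analysed by receipt. If assignment is used there is no bias. If the coding sentence is followed literally, intention-to-treat is lost and a null support component would show an odds ratio of about 0.25–0.33, given 30–50% triggered and suppression of 40% against 80%. A useful component could appear harmful: in the simulation, 1.23–1.35 by assignment became 0.65–0.77 by receipt. Both the size and the reversal rest on assumed rates. The S2 problem rests on no assumption. The interaction scale is a labelling matter only.

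**What to change.** Replace the coding sentence with wording such as: each component is coded +1 if the participant's randomised condition assigns it on (for S2, enhanced) and −1 if off (for S2, basic), whether or not the component was triggered or delivered. Add that any analysis based on actual receipt is secondary and labelled as such.

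Optionally, state that for a two-way interaction Exp(2 × coefficient) is the square root of the ratio of odds ratios, which is Exp(4 × coefficient).

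The cost is a sentence or two of wording. Design, data collection and sample size do not change. The wording should be settled before outcome data are analysed.

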#### Outcome measures

We will be collecting data using viral load results (at month 4 and month 12—obtained from patient records and the National Health Laboratory Service online system), EAMs (daily), pharmacy refills (monthly), and participant and staff surveys. The primary outcome will be viral suppression at month 24 post-enrollment as measured by plasma HIV-1 viral load <50 copies/mL. Secondary outcomes will include viral suppression at month 12, change in viral load over time, and total days of unsuppressed virus during study participation. Additional secondary outcomes include the following: mean electronic adherence and percent of participants ≥90% and ≥80% adherence in months 12 and 24; mean adherence over months 1–12 and 1–24; retention in ART care (percent of participants attending all refill visits within 7 days for monthly refills and 14 days for longer refill intervals) over months 1–12 and 1–24; percent of participants attending ≥75% refill visits (within 7 days), over months 1–12 and 1–24; percent of participants lost to care, defined as no clinic contact for ≥12 weeks at month 24); and time to suboptimal adherence detection and linkage to support (number of days from month 0 to day identified as nonadherent, as per the definition used in their intervention; number of days from month 0 to linkage to ROTF support).

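### Change in viral load from month 0 is assigned to linear regression with no month-0 term or scale named; adding log10 month-0 viral load would gain precision at no cost on this secondary outcome

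*Protocol article*

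**What the plan says.** Outcome measures lists the outcome among the secondary ones: "Secondary outcomes will include viral suppression at month 12, change in viral load over time, and total days of unsuppressed virus during study participation". Data and statistical analysis gives the model, "We will use linear or Poisson regression to estimate effects of components on outcomes measured as a continuous variable", and offers "mean change in viral load from month 0 to 12 and month 0 to 24" as the example; Poisson is for counts. That section also sets out the effect coding and the exchangeable correlation by clinic. It lists no covariates for any model, and it does not say whether viral load is analysed in copies/mL or on the log10 scale.

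Two other statements bear on the point. Under Eligibility criteria, participants are people "who are presenting to the clinic for initiation of ART", so a month-0 value is a pre-treatment value. Under Sample size, the trial is planned on "using the baseline HIV viral suppression rate of 60%, endline rate of 74" per cent. In people starting ART, the first of those rates can only be the rate expected at follow-up without the component, not suppression at month 0.

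The primary outcome is separate: "The primary outcome will be viral suppression at month 24 post-enrollment as measured by plasma HIV-1 viral load <50 copies/mL". It is binary and uses no change score.

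**The concern.** If 60-74% of participants end below 50 copies/mL, their follow-up values sit at or near the assay limit and hardly differ. Their change scores then differ mainly because their starting values differed. Randomisation makes those starting values independent of the component, so this variation says nothing about its effect and widens the standard error.

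Without a month-0 term, the viral load analysis could fail to show an effect of the size the trial is designed to detect. A null viral load result might then stand beside a positive suppression result for the same component. The stake is precision and ease of interpretation on a secondary outcome.

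**Working it through.** **The plan's own figure.** For 60% v 74%, two-sided 0.05 and 80% power:

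n per group = [1.96·√(2·0.67·0.33) + 0.842·√(0.60·0.40 + 0.74·0.26)]² / 0.14² = 176.

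Multiplying by 1 + (3 − 1)·0.15 = 1.3 gives 229 per group, 458 in total, as stated. Dividing by 0.9 gives 509, against the stated 510. This concerns binary suppression and does not depend on the present point. The article states no SD, correlation or power for change in viral load.

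**General formula.** Let k = SD(month 0)/SD(follow-up) and ρ = their correlation. Then

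VR = variance(unadjusted change) / variance(baseline-adjusted) = (k² + 1 − 2ρk)/(1 − ρ²).

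VR is never below 1 and equals 1 when ρ = k. Examples:

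- k = 0.5: 1.25 (ρ = 0), 1.04 (0.3), 1.00 (0.5)
- k = 1: 2.00, 1.54, 1.33
- k = 2: 5.00, 4.18, 4.00

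**Assumed inputs, log10 scale.** Baseline mean 4.5, SD 0.7, 0.9 or 1.1. Suppressed values set at log10(50) = 1.70. Unsuppressed mean 4.0, SD 1.0, correlation 0.5 with baseline. Suppression 60% v 74%, at first unrelated to baseline. 229 per level of one component, clinic clustering ignored.

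- Component effect: 0.14 × (4.0 − 1.70) = 0.14 × 2.30 = 0.322 log10.
- Follow-up variance within level: 0.24·2.30² + 0.40 = 1.67 and 0.1924·2.30² + 0.26 = 1.28; average 1.475, SD 1.214.
- ρ = 0.5 × (0.40 + 0.26)/2 ÷ 1.214 = 0.136.
- Adjusted variance: 1.475 × (1 − 0.136²) = 1.448; SE = √(4 × 1.448/458) = 0.112; power = Φ(0.322/0.112 − 1.96), about 82%.

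| Baseline SD | k | VR | Variance cut (1 − 1/VR) | SE, change | Power, change |
|---|---|---|---|---|---|
| 0.7 | 0.58 | 1.20 | 16% | 0.123 | 74% |
| 0.9 | 0.74 | 1.37 | 27% | 0.132 | 69% |
| 1.1 | 0.91 | 1.60 | 38% | 0.142 | 62% |

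Simulation on the same inputs agrees within a few points: 64-75% for the change score and 81-84% adjusted.

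**Letting baseline predict suppression.** With baseline SD 0.9 and a higher baseline lowering the odds of suppression (simulated):

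| Log-odds slope per baseline SD | Overall ρ | Variance cut | Power, change v adjusted |
|---|---|---|---|
| 0 | 0.13 | 27% | 67-69% v 81-82% |
| 0.3 | 0.25 | 19% | 73% v 82% |
| 0.5 | 0.32 | 14% | 78% v 83% |
| 0.7 | 0.38 | 10% | 82% v 85% |
| 1.0 | 0.45 | 6% | 85% v 87% |

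The formula agrees for the last row: with k about 0.67 and ρ = 0.45, VR = (0.449 + 1 − 0.603)/(1 − 0.2025) = 1.06, a cut of about 6%.

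**Copies/mL.** A separate simulation used 256 v 256 and an unsuppressed residual SD of 0.8. The variance ratio was about 1.8 at a baseline SD of 0.6 log10, and far above 10 at 0.9 or more. Power was about 3-6% for the change and only 12-15% after adjustment. On this scale adjustment alone does not rescue the analysis, so the scale has to be stated as well.

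**Change score or follow-up value.** Let F be the follow-up value, B the month-0 value and x the component. If F = a + b·x + c·B + e, then F − B = a + b·x + (c − 1)·B + e. The estimate of b and its SE are identical; only the coefficient of B moves, by 1.

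**The case against.** The strongest reply is that the article nowhere says the regression is unadjusted. It gives an outcome and a model family inside an example, with no covariate list for any analysis, and an analysis plan that is not shown may already contain the month-0 term. That stands: a reader might infer that an unadjusted analysis is prescribed, and the text does not support it. What remains is that outcome and model are stated, and the one term that matters most for them is not.

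A reader might also infer that baseline variation swamps the estimate. That description fits only copies/mL, a scale the article does not state. On log10 the loss is moderate, and it shrinks to a few power points if baseline predicts suppression. Nor need the change score be abandoned: with month 0 in the model it gives the same component estimate. Bias is not at issue, because components are randomised.

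A practical objection is that month-0 values may not be available. Outcome measures names "viral load results (at month 4 and month 12—obtained from patient records" without month 0. But that list also omits month 24, when the primary outcome is measured, so it is not complete, and the schedule figure is not shown. In any case the stated outcome cannot be computed without a month-0 value, so adjustment asks for nothing more.

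Finally, the optimization objective defines efficacy by viral suppression and retention, so change in viral load does not itself drive the choice of components. That stands, and it limits the importance of the point.

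**Conclusion.** The point holds as a precision improvement to a secondary outcome. An unadjusted change score would be unbiased and valid, but never more precise than the baseline-adjusted estimate. Adjustment cuts the log10 variance by about 16-38% over baseline SD 0.7-1.1 if suppression is unrelated to baseline, and by as little as about 6% at SD 0.9 if the relation is strong. Every one of these figures rests on assumed SDs and correlations, since the article gives none; with other values the gain could be nil (ρ = k) or larger. If copies/mL were used, baseline noise would dominate. The documents do not support any stronger conclusion: no error of bias, no effect on the primary outcome, and no effect on the 458 or 512. This is a minor improvement worth making.

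**What to change.** In Data and statistical analysis, state that log10 viral load at months 12 and 24, or its change from month 0, is regressed on the effect-coded components with log10 month-0 viral load as a covariate. State that values below 50 copies/mL are set at the limit or treated as censored. If they are treated as censored, take the follow-up value as the outcome, since the limit applies to that value. Report the adjusted difference per component, which under the −1/+1 coding is twice the coefficient. If the analysis plan already says this, a clarifying sentence in the protocol is enough.

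The cost is wording only: no new data, visits or participants, provided the month-0 values that the outcome already requires are collected.
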